## Abstract

**Background:**

Although Colorado is perceived as a healthy state, in 2010, 14.1 % of children aged 2–5 were overweight and 9.1 % were obese. Despite the high prevalence of obesity in this population, evidence to support particular strategies to treat obese preschoolers is lacking. The efficacy of home-based, childhood obesity interventions to reduce a child’s body mass index is inconclusive. However, this model uniquely provides an opportunity to observe and intervene with the home food and activity environment and engage the entire family in promoting changes that fit each family’s unique dynamics.

**Methods/design:**

Eligible participants are children aged 2–5 years who attended a well-child care visit at a Denver Health Community Health Service clinic within 12 months prior to recruitment and on that visit had a body mass index (BMI) >85th percentile-for-age. Participants are randomly recruited at study inception and allocated to the intervention in one of five defined 6-month stepped wedge engagements; the delayed intervention groups serves as control groups until the start of the intervention. The program is delivered by a patient navigator at the family’ home and consists of a 16-session curriculum focused on 1) parenting styles, 2) nutrition, and 3) physical activity. At each visit, a portion of curriculum is delivered to guide parents and children in selecting one goal for behavior change in each of three work areas to work on during the following week. The primary study outcome measure is change in BMI z-score from baseline to post-intervention period.

**Discussion:**

This childhood obesity study, innovative for its home-based intervention venue, provides rich data characterizing barriers and facilitators to healthy behavior change within the home. The study population is innovative as it is focused on preschool-aged, Latino children from low-income families; this population has not typically been targeted in obesity management assessments. The home-based intervention is linked to clinical care through update letters and assessment of the program’s impact to the child’s medical providers. Informing primary care providers about a child’s accomplishments and challenges, allows the clinician to support the health weight effort when seeing families during subsequent clinical visits.

**Trial registration:**

ClinicalTrials.gov NCT02024360 Registered December 21, 2013

## Background

Childhood obesity in the United States has reached an alarming prevalence rate, affecting all age groups including preschool children [1–3]. Obesity in children aged 2–5 years has increased from 5 % in 1971–1980 to 10.4 % by 2000 [2] to 12.1 % by 2009–2010 [4]. While several reports [5–7] describe improving obesity trends, Colorado rates continue to increase with the nation’s second highest rate of childhood obesity increase [7, 8]. In 2010, 14.1 % of Colorado’s children aged 2–5 years were overweight and 9.1 % were obese [9]. Poverty, an important social determinant of health, correlates significantly with obesity. In 2014, 18 % of children in Colorado lived in poverty, with Denver County having an even higher rate (29 %) [10].

Despite high preschooler obesity prevalence, evidence to support particular treatment strategies is lacking and convenient access to community-based treatment is limited [11]. While previous treatment studies often excluded children younger than 6 years of age [12], recent data suggest greater treatment success among preschool aged children than older children [13–16]. The US Preventive Services Task Force (USPTF) has recommended that primary care providers screen for and then refer obese children over 6 years of age to high quality treatment programs; no obesity screening recommendations were made for children younger than 6 years due to relatively limited treatment offered to this age group [17]. Testing treatment protocols for preschool children may build evidence for future screening recommendations for young children. Ideal protocols would be feasible, cost-effective, and reach low-income and minority children, who are at greatest risk for persistent obesity.

Research suggests that patient navigators and lay health workers can improve outcomes for chronic disease in adults [18–20] and children [21] and are effective in facilitating behavior change in various settings [22]. The efficacy of home-based, childhood obesity interventions to reduce children’s body mass index (BMI) is unknown [15, 23]. The home-based model is unique by providing an opportunity to observe and intervene with the home food and activity environment [13, 15, 23, 24]. In addition, family-based obesity interventions involving the child and the parent are associated with positive outcomes since families treated together share common treatment goals [25–27]. When the caregiver is included in obesity management programs [28, 29], families have demonstrated changed behaviors; intensive lifestyle and parenting skills education has resulted in sustained weight loss [30–33].

The Community Outreach Obesity Prevention Trial (COOPT) is an ongoing, 4-year (October 2011-September 2015) randomized controlled trial that tests the effectiveness of a home-based patient navigator program delivered to preschoolers of a large urban safety-net health care system. The intervention targets children aged 2–5 years within a predominantly Latino population. The primary goals are to examine the effect of the intervention in reducing the BMI z-score in the patient and the changes in health behaviors using the “5-2-1-0” daily targets (i.e., 5 fruits and vegetables, less than 2 hours screen time, 1 hour or more of exercise and 0 sweetened drinks) [34] using a home-based, patient navigator-mediated childhood obesity intervention.

COOPT is delivered by patient navigators at a family’s home. By focusing the program on the family unit, the parent sets goals for the child taking into account family dynamics around nutrition and physical activities. Primary care providers often lack the time to offer intensive weight counseling to families since the average well child visit is less than 20 minutes [35], and many providers do not feel they have the tools or knowledge to provide adequate weight management counseling [36, 37]. This intensive 25-hour program provides [38] a home-based platform for patient navigators to offer hands-on opportunities for skill-building, provide detailed education and counseling to families, reinforce learned concepts throughout the intervention, and offer opportunities for families to set, evaluate, and modify goals, as necessary.

**Fig. 1 Fig1:**
[figure not shown]
Flow of Children into the Study: Randomization, Recruitment, Enrollment, and Intervention Processes, Denver Health, 2012-2015

The primary outcome measure is BMI z-score over time in children receiving the intervention compared to waitlist controls (delayed intervention). We hypothesize that children receiving the intervention will have a greater reduction in BMI z-scores than children in the waitlist control group. We will compare the change in BMI z-score slope of the two groups from baseline to follow-up period. The follow-up period of the intervention group is from the start through the end of the intervention. The follow-up period for the delayed intervention group is from recruitment to the start of the intervention.

The secondary outcome is change in health behaviors using the “5-2-1-0” daily targets (i.e., 5 fruits and vegetables, less than 2 hours screen time, 1 hour or more of exercise, and 0 sweetened drinks). We hypothesize that children receiving the intervention will experience a greater improvement in “5-2-1-0” measures from baseline to post-intervention compared with children in control group. A thorough evaluation of the delivery processes and acceptance by stakeholders will inform the potential for implementation and dissemination of the intervention.

### Study setting and participants

Denver Health [39] (DH), an integrated urban safety net health system, includes a 477-bed hospital, 16 school-based clinics, and eight federally qualified community health centers. DH provides services to 25% of Denver residents, 35% of Denver’s children, and a large proportion of indigent and minority populations (58% Latino, 21% Caucasian, 17% African American; 4% other races). Among DH primary care patients, 98% are below 200% of the federal poverty guidelines and most (87%) are publicly insured or uninsured patients. In 2013, among 42,521 children 2–18 years old seen at DH, 32% (13,944) were overweight or obese; of whom, nearly 11,000 (79%) were Hispanic or Latino.

Eligible participants for the study are children aged 2 to 5 years who have been receiving well-child care at a Denver Health Community Health Service clinic for at least 12 months, had two or more visits with the most recent visit within 18 months, and have a BMI >85th percentile-for-age, recorded at least 9 months prior to the effort to recruit. Children with a physical or developmental disability/condition that precludes measurement of standing height, or a chronic (i.e., greater than 1 month) physical or developmental disability/condition that precludes age-appropriate participation in routine physical activity are excluded.

This study was approved by the Colorado Multiple Institutional Review Board (Protocol 11–1700).

### Recruitment and randomization

Participant recruitment is performed from a randomized list of overweight or obese patients who had a BMI measure recorded at least 9 months prior to study initiation (Fig. 1). Biologically implausible values for height or weight are excluded using a CDC-developed algorithm [40]. A research assistant contacts potential enrollees from the randomized list. Prior to the call, families are mailed a postcard with a brief description of the program and informed that they will soon be contacted. Once called, a bilingual English-Spanish research assistant explains the study to the family over the phone. If the family agrees to participate, the research assistant reads a verbal consent and documents consent. After oral consent is obtained, a baseline set of behavioral questions is administered. The survey is re-administered if more than 30 days have lapsed between the administration of the baseline survey and the start of the intervention. These baseline pre-intervention behaviors are compared with post-intervention and 6-month post-intervention behaviors recorded on subsequent questionnaires.

Study participants are told they will be scheduled to begin patient navigator visits in a staggered manner, using a stepped-wedge design [41] with individuals assigned to an intervention cohort to start the intervention. Those not enrolled in the initial intervention cohort are sent quarterly newsletters with information and resources unrelated to the intervention to keep participants connected to the study, during the delayed period.

### Intervention

At the beginning of the intervention, the patient navigator contacts a cohort of previously recruited families to schedule the first home visit. The first home visit is aimed at creating a positive rapport between the caregiver and the patient navigator and to set program expectations and goals. At this visit, the patient navigator sets lifestyle change and weight goals with families. The following talking points are used to explain the program’s goals to families: 1) program goal is to help your preschooler grow at a healthy rate which means your child’s weight will be matched well for height; 2) pre-school children who carry too much weight for good health can gradually become healthier by slowing the rate of weight gain and then holding their weight steady; 3) as your child grows taller the weight will better match the height and the risk of illnesses like diabetes and heart disease are expected to be lower than if the child remains obese into adulthood; 4) rarely should we expect preschoolers to lose weight, if they do, losing no more than one pound per month can be healthy and weight loss is usually not needed unless preschoolers are severely overweight; and 5) the best way to help preschoolers grow healthier is to practice healthy eating and exercise habits as a whole family. At this initial visit, the patient navigator administers a written consent, and a copy of the consent forms are provided to each family.

At each subsequent home visit, the patient navigator delivers a portion of the curriculum focused on parenting styles, nutrition, and/or physical activity to guide parents and children in selecting one goal for behavior change in each of the three areas to work on the following week. Families report progress towards these goals at the following session. Patient navigators exercise flexibility to change the order of the sessions, spending more or less time on a topic tailored to the family’s level of understanding or mastery of skills. The full curriculum content is delivered regardless of the order of the sessions. Home visitation sessions usually occur on weekdays before 7:30 pm; occasionally the visits occur on Saturdays to accommodate the families’ schedules. The entire family, including siblings 3–18 years of the index overweight or obese child, is invited to participate in the sessions.

A nurse-practitioner, leader of clinical obesity services for the Denver Health Community Health Services, is liaison to facilitate interactions between patient navigators and clinicians. Health care providers of the children participating in the program receive three letters throughout the program: 1) at enrollment, informing that the child started the program, 2) at mid-intervention, listing the child’s progress and goals, and 3) at completion, summarizing the child’s accomplishments, future goals and challenges in achieve current goals. These letters inform the provider during subsequent clinical visits to engage in discussion to support the family’s achieving goals set with the patient navigators during the program.

### Curriculum

The curriculum used in this program was extensively adapted from a family-centered, telephone-delivered, childhood obesity treatment program developed by Kaiser Permanente “Family Connections”[42]. The curriculum was roughly doubled in intensity and translated into 16 home/community visits that occur over a 25-hour period. The choice of curriculum components and mode of delivery was purposeful. To ensure cross-cultural acceptance of the intervention, the American Diabetes Association Latino Outreach Program was consulted during program adaptation. With assistance from the Latino Outreach Program, two focus groups with mothers and grandmothers of preschool aged-children were conducted. Based on feedback from the focus groups, curriculum tracks on parenting skills, helping preschoolers accept healthy foods, and hands-on cooking and shopping skills were added to the “Family Connections” curriculum by clinical experts who are part of the COOPT program.

The program curriculum focuses on nutrition, physical activities, and parenting skills delivered in the participant’s home (Table 1). Topics include parenting styles (e.g. limit setting, conflict resolution) and skills for facilitating healthy behavior change (e.g. goal setting, troubleshooting, positive reinforcement) for parents of preschoolers. Nutrition education focuses on selecting healthy foods and healthy portions for the entire family. During family visits children participate in discussions designed to educate them about healthy foods (i.e., fruits, vegetables, whole grains, and lean proteins), at their developmental level.

**Table 1 Tab1:** Community Outreach Obesity Prevention Trial: Curriculum learning objectives

Session no.	Theme	Learning objectives:
1	Develop Rapport, Baseline Measurement; Explain 5-2-1-0 and Track Behaviors	1. Create rapport between family and navigator
		2. Family will be able to explain the study process and purpose
		3. Collect Baseline Data (Baseline measures)
		4. Explain 5-2-1-0 concepts
		5. Describe reasons for children’s growth patterns
		6. Describe your own family health behaviors
		7. Demonstrate how to keep track of behaviors and set goals
2	Nutrition: Focusing on family meals	8. Explain the structure for visits
		9. Explain 5-2-1-0 : focus on 5
		10. Describe 2 strategies for improving fruit and vegetable consumption
		11. Demonstrate rule setting around eating and food choices
		12. List a specific family challenge
		13. Describe how to keep track of behaviors and set goals
3	Physical Activity: Introduction	14. Explain “5-2-1-0”: 1 hour or more of physical activity every day
		15. Explain “5-2-1-0”: 2 hours or less recreational screen time per day
4	Being in charge and making changes	16. Describe a parent’s role during meal times
		17. Explain concept of food neophobia
		18. Describe use of differential attention (praising/ignoring)
5	Being a good judge of home health	19. Explain “5-2-1-0”: zero sugary drinks every day
		20. Explain why a home health assessment is valuable
		21. Compare PN and parent home health assessment results
6	Being focused on choices	22. Explain how to read food labels
		23. Describe whole grains, fiber
		24. Compare nutritional value of selected foods
		25. Explain what lean protein means and what foods contain them
		26. Describe low-fat dairy products and how to include in your meal planning
7	Grocery Store Outing	27. Demonstrate reading food labels
		28. Demonstrate comparison shopping and calculate unit pricing
		29. Describe ways to buy fruits and vegetables on a limited budget
8	Cooking Demonstration	30. Describe the method of preparing a new food or recipe(s)
		31. List beneficial factors from new recipe(s)
		32. Compare this recipes nutritional value to a similar but less nutritious form
		33. Demonstrate kitchen skills required to prepare the recipe(s)
		34. Plan a meal considering food preferences
9	Identifying barriers and Staying Motivated	35. Demonstrate exercising while delivering other objectives (walk during session)
		36. Describe the common barriers to regular exercise
		37. Describe the process of building motivation for physical activity
10	Creating a healthy home and effective directions	38. Describe how to set a home for success, eliminating food with little nutritious value, putting foods out of site
		39. Explain how to give effective directions to your child
11	Family Support: Promoting healthy body image and discipline	40. Explain how we talk promotes and affects a healthy body image
		41. Describe the use of time out and other discipline techniques
12	Nutrition: Fruits, Vegetables and Portion Control	42. Describe the importance of promoting fruits and vegetables with every meal
		43. Explain the value of snacks and nutritional goals
		44. Explain how to prepare healthy affordable meals
		45. Demonstrate ability to prepare healthy affordable meals
13	Physical Activity: Overcoming Burnout or Motivating Self or PA	46. Explain what burnout means and how it can be avoided
		47. Explain the importance of dealing with changing schedules
		48. Describe ways to maintain focus but be flexible
14	Family Support: Finding support and putting it all together	49. List ways to include other family and friends
		50. Demonstrate ability to blend all learned skills
15	Family Support: Planning Ahead and Problem Solving	51. Describe the home change experience
		52. Explain efforts for home change
		53. Describe methods to plan ahead for challenges
		54. Describe problem solving skills and their use
16	Final Measures	55. Celebrate Success, Allow for Review and Reflection

To supplement the curriculum with pre-school specific physical content and activities, the SPARK curriculum and activity set [43] was purchased for use by the patient navigators.

The curriculum also includes 1) a grocery store tour in which the patient navigator guides a family in selecting low-cost healthy foods and 2) a cooking session when the family and the patient navigator prepare a dish that is enjoyed by the family using healthy ingredients. Families receive a 10 dollar grocery gift card for the grocery store tour.

The curriculum is delivered to each family by one consistent bilingual patient navigator in the parent’s preferred language (English or Spanish).

### Patient navigator training

The program employs two full-time bilingual English-Spanish patient navigators. Patient navigators receive extensive training shortly after being hired. A four-day course sponsored by the NIH-funded, Colorado Clinical Translational Sciences Institute provides Patient Navigator Fundamentals [44] that includes patient communication, health promotion, professional conduct and motivational interviewing. The course is designed to equip individuals with the knowledge and skills necessary to function as a patient navigator. Specific childhood obesity knowledge is achieved by attending and observing a childhood obesity program curriculum (similar to the one offered through this program) yet delivered to groups in a community recreation center setting; patient navigators also have direct one-on-one training with experienced clinicians and patient navigators. Additional training components include in-home observations of patient navigators and debriefing and evaluation sessions with an experienced [45–47] patient navigator supervisor.

### Outcome measures

#### Child measures

##### Height and weight

The primary outcome of the study is the child’s BMI z- score over time, used to assess change in BMI z-score from baseline to follow-up. Height and weight are measured at the first and last home visits. Standing height is measured with the child barefoot. Patient navigators are taught measurement techniques by experienced medical assistants in community pediatric clinics, overseen by study team nurse practitioner. To ensure accurate measurement in each session, height is measured three times and the average value is recorded. Children are weighed in light clothing, without shoes. Weight and height are measured on a LifeSource™ UC-321 Precision Scale and Charder HM200P Portstad Stadiometer. BMI percentile and BMI z-scores are calculated using age and sex-specific information based on the 2000 Center for Disease Control (CDC) growth charts [40].

##### Diet and physical activity

The physical activity and eating behaviors of the child as summarized in “5-2-1-0” daily targets are captured by a standard survey [48] administered to the child’s caregiver at the time of recruitment, at the completion of the intervention and at 6-months post-intervention. Families receive a 10 dollar gift card for each completed survey.

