### Enrollment and retention efforts

Assistance from the child’s primary care provider is sought to improve program enrollment and retention. For families who decline to participate despite previously agreeing, or families who drop-out of the program after attending some sessions, the clinician liaison contacts the child’s provider and asks for permission to send a language-concordant letter to the child’s caregiver, on behalf of the clinician, encouraging program participation or completion.

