#### Secondary analysis

To determine intervention effect on patient physical activity and eating behaviors, we will compare the mean “5-2-1-0” index from baseline to post-intervention using the paired *t*-test. Additional analyses will be carried out using general linear mixed models with repeated measures on children to adjust for covariates and explore possible baseline predictors of change.

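### The 5-2-1-0 survey times hang on starting and completing the programme, and the outcome section omits the only survey that gives waiting families a second value

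*Protocol article*

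**What the plan says.** All references are to the protocol article.

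- **Outcome measures, Diet and physical activity** gives three survey times: "at the time of recruitment, at the completion of the intervention and at 6-months post-intervention".
- **Recruitment and randomization** adds a fourth, conditional one: "The survey is re-administered if more than 30 days have lapsed between the administration of the baseline survey and the start of the intervention". It continues: "These baseline pre-intervention behaviors are compared with post-intervention and 6-month post-intervention behaviors recorded on subsequent questionnaires".
- **Overview and hypotheses** (text after Fig. 1) states a between-group hypothesis for this outcome: "greater improvement in “5-2-1-0” measures from baseline to post-intervention compared with children in control group". The observation windows are defined there for the primary outcome. For treated children: "The follow-up period of the intervention group is from the start through the end of the intervention". For waiting children: "The follow-up period for the delayed intervention group is from recruitment to the start of the intervention".
- **Secondary analysis** plans a within-child test: "we will compare the mean “5-2-1-0” index from baseline to post-intervention using the paired" t-test. Mixed models with repeated measures follow, for covariate adjustment and predictors of change.
- **Enrollment and retention efforts** foresees families who agree and later decline, and also "families who drop-out of the program after attending some sessions". The only response described is an encouragement letter sent on the clinician's behalf.

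**The concern.** A waiting family contributes to the behavioural comparison only if it has a value at recruitment and another at the end of its wait. The section that defines the outcome provides no such second value. The section that does provide it ties the survey to the start of the intervention. On the treated side, the second value is tied to completion, and the 6-month value counts from there.

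If the surveys are run as written, a family that declines when its turn comes gives no end-of-wait value, and a family that stops part-way gives no post-intervention value. The children compared would then be chosen partly by behaviour after randomisation. Change in health behaviours stands among the primary goals in the Background, so the outcome is not peripheral. A survey that was never given cannot be recovered by any later analysis.

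**Working it through.** **The plan's own figures.** No drop-out rate, effect size or standard deviation is given for 5-2-1-0. The one power figure (81%; 80 versus 160 children; effect size 0.39) concerns the BMI z-score. It reproduces at two-sided 0.05 (assumed): 0.39 × √(80 × 160/240) = 2.848; 2.848 − 1.960 = 0.888; power 81.3% (81.0% with the t distribution). It has no bearing on this point.

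**Which surveys exist for whom**

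| Family | Recruitment | Before start | After intervention |
|---|---|---|---|
| Starts and completes | yes | if more than 30 days have passed | yes |
| Starts, then stops | yes | if more than 30 days have passed | none scheduled |
| Declines at its turn | yes | none scheduled | none scheduled |

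Everyone is recruited at inception and enters one of five 6-month steps (Abstract; Overview and hypotheses). The 30-day condition is therefore met by essentially every delayed family. For the last cohort, recruitment and start lie about 4 × 6 = 24 months apart if the steps run back to back. Recruitment and pre-start values are thus far from interchangeable in children aged 2-5.

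**Within-treated change (the paired t-test).** Set the completers' mean change to 1. Let q be the share of treated families without the second survey, and r their change relative to completers. The mean over all families is (1 − q) + q·r, so the complete-pair mean differs from it by the factor 1/[(1 − q) + q·r]. Both q and r are assumptions.

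| q | r = 0 | r = 0.5 | r = 1 | r = 1.2 |
|---|---|---|---|---|
| 20% | 1/0.80 = 1.25 | 1/0.90 = 1.11 | 1.00 | 1/1.04 = 0.96 |
| 40% | 1/0.60 = 1.67 | 1/0.80 = 1.25 | 1.00 | 1/1.08 = 0.93 |

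**Control side (the between-group hypothesis).** Let waiting families who go on to start change by c, as a fraction of the treated change. Let a share k never start, with no change. With selection among controls only, the observed contrast is 1 − c and the true one is 1 − c(1 − k):

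- c = 0.1, k = 0.2: 0.90/0.92 = 0.98
- c = 0.3, k = 0.4: 0.70/0.82 = 0.85

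Control selection alone thus shrinks the contrast.

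**Both together**, with q = 0.2, r = 0, c = 0.2 and never-starters unchanged: the true contrast is 0.8 − 0.2(1 − k) and the observed one is 0.8.

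- k = 0: 0.8/0.60 = 1.33
- k = 0.2: 0.8/0.64 = 1.25
- k = 0.4: 0.8/0.68 = 1.18

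The two selections pull in opposite directions.

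**The case against.** **Completion may mean the scheduled end of the cohort's step.** Elsewhere the authors tie a measure to a visit explicitly (height and weight at first and last visits; home assessment at sessions 5 and 15) and speak of graduates when they mean finishers. The survey sentence does neither, and the baseline survey needed no home visit. So nothing forbids surveying families who stopped. That stands. But the provider letter at completion (Intervention) summarises the individual child's achievements, and the retention section uses the word for what drop-outs are urged to reach. The family-level reading is the more natural one.

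**The two survey sections are compatible.** This stands. A reader might infer two conflicting schedules, but one section gives standard times and the other adds a conditional repeat. It is an omission. Recruitment and randomization also suggests that the refreshed survey is the treated baseline, although Secondary analysis does not say so.

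**Following up drop-outs is detail that an article leaves to the full protocol.** This stands in part. The full protocol may settle it, but the article itself fixes the survey times, and fixes them by participation.

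**The mixed models keep children with incomplete surveys.** This is true under missing at random. However, a family with a recruitment survey only says almost nothing about change, and the paired test drops it.

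**The direction of bias is not documented.** This stands. A reader might infer that losses in both arms inflate the result. The documents do not show that families who stop improve less, and the control-side loss more likely works the other way.

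**Conclusion.** The point holds as a gap in the survey schedule with a risk of selection bias. It does not establish that the effect is overstated. As written, families who never start or who stop have no scheduled second 5-2-1-0 survey, and the outcome section omits the one survey on which the control side of the hypothesis depends.

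The size is unknown. Under an assumed 20-40% stopping, the within-treated change is inflated by a factor of 1.25-1.67 if stoppers retain none of the completers' change and 1.11-1.25 if they retain half. It is unbiased if they change equally and slightly understated if they change more. Control-side selection alone, under the assumptions above, would reduce the between-group contrast to 0.98-0.85 of its true value. This should be corrected: the outcome is secondary and the bias unquantified, but the remedy is cheap.

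**What to change.** 1. Add the pre-start survey to Diet and physical activity so that it agrees with Recruitment and randomization.
2. Tie the survey to the calendar of the allocated cohort: recruitment, scheduled start, scheduled end of the 6-month step, and 6 months later.
3. Give it by telephone to every recruited family, including those who declined, postponed or stopped, unless consent to contact is withdrawn.
4. Name the scheduled-start survey as the end-of-wait value for controls and as the baseline for treated time.
5. Analyse by allocated cohort, and report how many families in each cohort answered at each time.

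The cost is small: more calls by the existing research assistant and the existing 10 dollar card for each additional completed survey. The downside is that some families who stopped will not answer, so the selection is reduced and becomes visible but is not removed.
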